**Evaluation of effects**						
Musculoskeletal complaints (D-CMDQ)		**x**				**x**
Number of sick days (total, musculoskeletal)		**x**		**x**	**x**	**x**
Work armouring (NASA-RTLX)		**x**		**x**	**x**	**x**
Fatigue (FS)		**x**		**x**	**x**	**x**
Work-related psychosocial stress (COPSOQ)		**x**				
Job satisfaction (Item B11.7 COPSOQ)		**x**		**x**	**x**	**x**
Cognitive performance (Vienna Test System)^a^		**x**				
Resting heart rate^b^		**x**				**x**
Resting blood pressure^b^		**x**				**x**

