## Statistical methods

### Statistical methods for primary and secondary outcomes {20a}

Data will be analyzed using IBM SPSS Statistics (Version 29; IBM, Armonk, New York, USA). For the primary effectiveness analysis, both exoskeleton arms (Exo1 and Exo2) will be pooled into a single intervention group and compared to the control group. Exploratory analyses will additionally compare the three randomized arms separately. The primary analysis will follow an intention-to-treat (ITT) approach, meaning that all randomized participants will be analyzed in the groups to which they were initially assigned. Data from participants with missing information will be analyzed under the "missing at random" assumption. Per-protocol analyses will include only those participants in the intervention group who wore the exoskeleton at least 75% of the days each week when lifting tasks are performed. These analyses will be conducted as sensitivity analyses to assess the robustness of effectiveness-related estimates with respect to intervention adherence and wearing behavior. 

The primary applicability endpoint will be assessed descriptively. To evaluate the metric endpoints, mixed-effects models with a repeated measures structure will be estimated using restricted maximum likelihood. In this model, the measured values collected during all study visits will be considered the dependent variable. We will include treatment group (exoskeleton vs. control) and categorical time as fixed effects. Interactions between the group and time (categorical) will also be modeled. For random effects, we will include an intercept for each subject. Within the mixed models, we will estimate 95% confidence intervals (CIs) and *p*-values for contrasts between groups for the 3-month period. For sensitivity analyses, only patients with complete paired baseline and 3-month follow-up data will be included, ensuring a time difference within groups is analyzed using a paired *t*-test for dependent samples.

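### With a subject intercept as the only named covariance term, 95% intervals for change in the four-visit secondary outcomes are too narrow if within-person correlation fades over time

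*Protocol article*

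**What the plan says.** Statistical methods {20a} announces that "mixed-effects models with a repeated measures structure will be estimated using restricted maximum likelihood", in SPSS. In that model "the measured values collected during all study visits will be considered the dependent variable", so baseline is a response and not a covariate. The fixed effects are group and categorical time, and "Interactions between the group and time (categorical) will also be modeled". On within-person dependence the text gives one term: "For random effects, we will include an intercept for each subject". No residual covariance type is named. Intervals and p-values are promised for "contrasts between groups for the 3-month period".

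Table 3 schedules NASA-RTLX, FS and the COPSOQ job-satisfaction item at weeks 0, 4, 8 and 12. It schedules the D-CMDQ at weeks 0 and 12 only. Intervention description {11a}, however, lists musculoskeletal complaints among the constructs assessed every 4 weeks.

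**The concern.** A random intercept with independent residuals is compound symmetry: one correlation serves all six pairs of visits. Repeated workload, fatigue or satisfaction scores may well be more alike 4 weeks apart than 12 weeks apart. If so, the fitted common correlation lies above the true week-0-to-week-12 correlation. The model then understates the variance of the longest change, which is the contrast of most interest.

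The trial describes its effectiveness analyses as estimation, so the calibration of the 95% intervals is what a reader will rely on. What is at stake is overstated precision for three secondary outcomes. No confirmatory decision depends on it.

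**Working it through.** **Inputs from the protocol article.** Four visits at weeks 0, 4, 8 and 12 (Table 3); subject intercept, group, categorical time and group-by-time ({20a}); 80 and 40 complete datasets, and dropout of up to 50% ({14}). The protocol's own recruitment figure reproduces: 120/(1 − 0.5) = 240, that is 160 and 80. It gives no precision or correlation figure to reproduce.

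**Assumptions.** Equal variance at every visit, independent residuals around the intercept, and complete data for the formula. Correlations r1, r2, r3 apply to visits one, two and three steps apart. The documents give none, so a range is shown, starting from r1 = 0.70.

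**Formulas.** Four visits form six pairs: three at one step, two at two steps, one at three steps.

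- Mean correlation: m = (3·r1 + 2·r2 + r3)/6.
- Variance of a person's change according to the model: 2σ²(1 − m). True variance from week 0 to week 12: 2σ²(1 − r3).
- Ratio of model SE to true SE: q = √[(1 − m)/(1 − r3)].
- Coverage of the nominal 95% interval: P(|Z| < 1.96·q).

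Worked case, 0.70/0.60/0.50: m = (2.10 + 1.20 + 0.50)/6 = 0.633; q = √(0.367/0.500) = 0.856; 1.96 × 0.856 = 1.678; coverage 90.7%.

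| Fall per visit | r1 / r2 / r3 | m | q | Coverage |
|---|---|---|---|---|
| 0 | 0.70 / 0.70 / 0.70 | 0.700 | 1.00 | 95.0% |
| 0.02 | 0.70 / 0.68 / 0.66 | 0.687 | 0.960 | 94.0% |
| 0.05 | 0.70 / 0.65 / 0.60 | 0.667 | 0.913 | 92.6% |
| 0.10 | 0.70 / 0.60 / 0.50 | 0.633 | 0.856 | 90.7% |
| 0.15 | 0.70 / 0.55 / 0.40 | 0.600 | 0.816 | 89.0% |

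In SD units at 80 versus 40, the SE of the difference in change is √[2(1 − r)(1/80 + 1/40)]. For a fall of 0.05 per visit the true value is √(0.8 × 0.0375) = 0.173, against 0.158 from the model.

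**Simulation check of the stated model (REML).** With a first-order autoregressive pattern, adjacent correlation 0.7, and 80/40 complete, the empirical SE of the change contrast was 0.220, the model SE 0.179 and coverage 88.8%; the formula gives 88.7%. With 160/80 randomized and 50% dropout completely at random, coverage across three fading patterns was 87 to 90%. With truly equal correlation it was 95 to 96%, so the loss comes from the covariance assumption. For 0.70/0.55/0.40 at 80/40, simulated coverage was about 89% with the random intercept and about 95% with an unstructured covariance.

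**The other reading of the contrast.** For the group difference at month 3, the same simulations under fading gave 94 to 95% with complete data and about 94% with 50% dropout. That contrast depends mainly on the variance at one visit, which compound symmetry does not distort when variances are equal.

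**D-CMDQ.** Two visits give one pair, so m = r3 and q = 1.

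**The case against.** The strongest reply is that the protocol never says the residuals are independent. It mentions a repeated measures structure as well as the intercept, and in SPSS MIXED the RANDOM and REPEATED parts are separate, so a residual covariance may be intended and left to the analysis plan. This stands as a condition: with a residual structure that varies by lag, the problem disappears. It does not remove the point, because the intercept is a choice the text makes and nothing in the text relaxes what it implies.

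Second, the contrast is not pinned down. Change from baseline is defined as an endpoint only for the CMDQ ({12}), and the month-3 difference is nearly unaffected. This also stands. Change is still the more natural reading, because baseline is modelled as a response and {7} frames effectiveness as change.

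Third, the planned sensitivity analysis pairs baseline and 3-month data. That uses the observed change SD, but within groups, so it does not correct the between-group interval.

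Some stronger conclusions that a reader might infer are not supported:

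- **That the co-primary result is affected.** Under Table 3 the D-CMDQ has two visits and is not. It would be affected only if collected every 4 weeks as {11a} describes.
- **That coverage will be 89%.** This is the steepest decline in the table. Mild fading costs about one percentage point, and equal correlation costs nothing.
- **That later trials would be undersized.** With equal variances the per-visit SD is not understated. Only the model-implied change variance of these secondary outcomes is, and the endpoint labelled effectiveness-related is the CMDQ.

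**Conclusion.** The point holds in conditional form. As written, the model implies equal correlation at all lags. For NASA-RTLX, FS and the job-satisfaction item, the interval for the group difference in baseline-to-week-12 change is then too narrow if correlation fades. Over the assumed range the model SE is between 0% and 18% too small, and coverage runs from 95% down to 89%. The conclusion rests on independent residuals, a change contrast, equal variances and correlations that the documents do not give. It is a modest issue in secondary, non-confirmatory outcomes, but worth correcting because the model is stated and the replacement is nearly free.

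**What to change.** For outcomes with four visits, replace the subject intercept with an unstructured residual covariance across visits (SPSS MIXED, REPEATED with type UN). State that the reported contrast is the group difference in change from baseline to 3 months. Reconcile Table 3 with {11a} on how often the D-CMDQ is collected; if it is every 4 weeks, the same covariance should apply to it.

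The change is to wording and needs no new data. Four visits need ten covariance parameters (4 variances and 6 covariances), which 120 to 240 participants can support. The downside is slightly wider intervals and a small risk of non-convergence. The degrees-of-freedom method and a fallback structure can be left to the analysis plan.

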### Criteria for discontinuing or modifying allocated interventions {11b}

No modifications are planned for the allocated intervention. The aim of the study is to assess the practical applicability of the exoskeleton under real-world working conditions. Should participants wish to discontinue the intervention—for example, due to discomfort or other subjective complaints—such discontinuations will be considered important study outcomes. These decisions provide valuable insights into the acceptability and user experience of the exoskeleton.

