##### Co-primary effectiveness-related endpoint

The co-primary effectiveness-related endpoint is the change in musculoskeletal complaints from baseline to 3 months, assessed using the Cornell Musculoskeletal Discomfort Questionnaire (CMDQ) score, comparing the intervention group with the control group.

This endpoint will be analyzed using longitudinal models to estimate mean changes, effect sizes, and 95% confidence intervals. Given the feasibility focus of the trial, these analyses are intended to generate preliminary evidence and inform the design and sample size calculation of future adequately powered confirmatory studies. No formal multiplicity adjustment will be applied, as the trial is not powered for confirmatory testing.

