### Methods in analysis to handle protocol non-adherence and any statistical methods to handle missing data {20c}

Protocol non-adherence (e.g., early discontinuation of the intervention) will be documented and analyzed descriptively. Data from participants with missing values will be included under the assumption that the missing values are missing at random.

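### The complete-case sensitivity analysis tests change within each arm, so it cannot check the between-group estimate it is meant to support

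*Protocol article*

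**What the plan says.** The co-primary effectiveness endpoint is the change in the Cornell questionnaire (CMDQ) score from baseline to 3 months, "comparing the intervention group with the control group" (Co-primary effectiveness-related endpoint). The primary analysis pools the two exoskeleton arms and fits a mixed model with group, categorical time and their interaction. From it, "we will estimate 95% confidence intervals (CIs) and *p*-values for contrasts between groups for the 3-month period" (Statistical methods {20a}).

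The same section names two sensitivity analyses:

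- A per-protocol analysis, intended "to assess the robustness of effectiveness-related estimates with respect to intervention adherence and wearing behavior".
- A complete-case analysis, described as follows: "only patients with complete paired baseline and 3-month follow-up data will be included, ensuring a time difference within groups is analyzed". The test named for it is the paired t-test.

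On missing data, section {20c} states: "Data from participants with missing values will be included under the assumption that the missing values are missing at random". The sample size section {14} targets 80 complete datasets in the intervention group and 40 in the control group.

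**The concern.** A sensitivity analysis should estimate the same quantity as the primary analysis under different assumptions or in a different analysis set. This one changes the quantity. The primary model asks whether the arms differ in change; the paired t-test asks whether one arm changed.

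Two things follow. First, the complete-case check cannot do its job: whatever it shows, the reader does not learn whether the between-group estimate is stable among completers. Second, it invites a familiar misreading, in which one arm's change is significant, the other's is not, and the arms are taken to differ. Regression to the mean, seasonal workload or expectation can move both arms equally. Expectation is a live possibility here, since the trial is open-label with a self-reported outcome, and section {17a} acknowledges performance and detection bias in subjective measures. With twice as many completers in the intervention group, an equal change is more likely to reach significance there, so the misreading tilts towards the device.

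**Working it through.** **The plan's own figure.** Section {14} inflates for up to 50% dropout: 120/(1 − 0.5) = 240, 80/(1 − 0.5) = 160 and 40/(1 − 0.5) = 80. These match the stated 240, 160 and 80. The 80 and 40 complete datasets are therefore used as completer numbers below.

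**What each analysis estimates.** Write D for the change from baseline to 3 months, with true means μ_E (pooled exoskeleton) and μ_C (control).

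- Primary contrast: μ_E − μ_C.
- Paired t-test in the exoskeleton group: μ_E.
- Paired t-test in the control group: μ_C.

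Neither paired test has μ_E − μ_C as its target, and neither gives a confidence interval for it.

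**How often the paired tests mislead when the arms do not differ.** Set μ_E = μ_C, so the true effect is zero. Let dz be the common mean change divided by the SD of change. The document gives no SD or expected effect for this score, so dz is an assumption and is varied.

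The power of each two-sided 5% paired test comes from the noncentral t distribution with n − 1 degrees of freedom and noncentrality dz × √n. At dz = 0.3:

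- Exoskeleton: 0.3 × √80 = 2.68, power 0.755.
- Control: 0.3 × √40 = 1.90, power 0.457.
- The arms are independent, so P(exoskeleton significant, control not) = 0.755 × (1 − 0.457) = 0.41.
- The reverse pattern: 0.457 × (1 − 0.755) = 0.11.

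The whole range:

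| dz, same in both arms | Power, n = 80 | Power, n = 40 | Exoskeleton only | Control only |
|---|---|---|---|---|
| 0.1 | 0.14 | 0.10 | 0.13 | 0.08 |
| 0.2 | 0.42 | 0.23 | 0.32 | 0.14 |
| 0.3 | 0.76 | 0.46 | 0.41 | 0.11 |
| 0.4 | 0.94 | 0.69 | 0.29 | 0.04 |
| 0.5 | 0.99 | 0.87 | 0.13 | 0.01 |
| 0.6 | 1.00 | 0.96 | 0.04 | 0.00 |

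A simulation of 20,000 trials per setting gave 33%, 41%, 29% and 13% for the exoskeleton-only pattern at dz 0.2, 0.3, 0.4 and 0.5. A two-sample t-test on the same simulated changes rejected in 4.9% to 5.3% of trials, which is its nominal error rate.

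**The case against.** **The primary analysis is sound, and the trial is not confirmatory.** The mixed model estimates the right contrast with a confidence interval, the protocol stresses estimation over testing, and nothing says the paired tests will support a between-group claim. All of that stands, and it limits the consequence: a misleading pattern would have to be read over the planned primary contrast. It does not rescue the check. In an estimation-focused trial, a sensitivity analysis that yields no between-group estimate or interval is of even less use.

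**The 0.41 is the peak of the range.** This also stands. At small or large common changes the probability falls to 0.13 or 0.04, so the range should be quoted and not the peak alone.

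**A reader might infer a second fault: that the plan leaves the missing-at-random assumption untested although half the data may be lost and workers stop because of symptoms.** The document does not support this as an error, for these reasons:

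- An analysis under departures from missing at random is commonly left to a statistical analysis plan, which is not shown here.
- The passage on stopping "for example, due to discomfort or other subjective complaints" (section {11b}) concerns discontinuing the intervention. A worker who stops wearing the device can still complete the 3-month questionnaire and stays in the intention-to-treat analysis.
- The 50% is a planning maximum; the feasibility target is dropout of at most 25%.
- The primary model is not restricted to completers.
- Any bias figure rests on an assumed shift. If missing exoskeleton-arm scores were 0.2 to 0.5 SD worse than predicted, with no shift in control, the bias would be 0.5 × 0.2 = 0.10 to 0.5 × 0.5 = 0.25 SD at 50% dropout, and 0.25 × 0.2 = 0.05 to 0.25 × 0.5 = 0.125 SD at 25%. With equal shifts and equal dropout in both arms it would be zero.

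**Conclusion.** The point holds for the complete-case analysis. Section {20a} itself specifies a within-group paired t-test as a sensitivity analysis for an endpoint defined between groups. This is a stated rule aimed at the wrong quantity, not a detail left for later, and an analysis plan could correct it only by departing from the protocol.

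If both arms change equally, the planned tests show significance in the exoskeleton group alone with probability 0.04 to 0.41 for dz between 0.1 and 0.6, against about 5% rejection for a between-group test. These figures assume 80 and 40 completers, normally distributed changes and equal SDs. The number with both baseline and 3-month scores may be larger, because the protocol's complete dataset also requires the 1-month and 2-month visits. That the test targets the wrong contrast does not depend on any of these assumptions.

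The primary estimate is not affected, and the handling of missing data is not shown to be wrong.

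**What to change.** In section {20a}, replace the paired t-tests with a between-group complete-case analysis: ANCOVA of the 3-month D-CMDQ score on pooled arm, baseline D-CMDQ and the stratification factors (sector, site and sex), pooling sparse sites. Report the adjusted difference with its 95% confidence interval beside the primary estimate. Show within-arm changes descriptively, without p-values.

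As an optional addition, a delta-adjusted analysis could shift missing 3-month scores over a stated range, at whatever dropout occurs between the 25% target and the 50% maximum. If an analysis plan already holds one, nothing more is needed.

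The cost is minor rewording and a little programming. No new data are needed and the sample size is unchanged. Recruitment is expected to run to June 2027, so there is time to make the change before database lock.

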### Interim analyses {21b}

No interim analysis is planned.

### Methods for additional analyses (e.g., subgroup analyses) {20b}

In exploratory analyses, the original three randomization arms will be entered as fixed effects. Additional exploratory subgroup analyses may be conducted to investigate differences in outcomes between sectors (logistics vs. healthcare), or by participant characteristics such as age or sex. These analyses will be reported as exploratory.

### Methods in analysis to handle protocol non-adherence and any statistical methods to handle missing data {20c}

Protocol non-adherence (e.g., early discontinuation of the intervention) will be documented and analyzed descriptively. Data from participants with missing values will be included under the assumption that the missing values are missing at random.

### Plans to give access to the full protocol, participant-level data, and statistical code {31c}

Upon reasonable request, access to the full study protocol, anonymized participant-level data, and statistical analysis code will be made available after publication of the primary study results. Requests will be reviewed by the study steering committee to ensure compliance with ethical and legal data protection requirements.

### Composition of the data monitoring committee, its role and reporting structure {21a}

No independent data monitoring committee (DMC) is established for this low-risk study. All procedures, including the development of the study protocol, the case report form, the content of participant information and consent, the application for ethics approval, data processing, central and on-site monitoring, and analyses, follow standard operating procedures (SOPs). The coordinating center is the Chair of Human-Technology Interaction, Magdeburg-Stendal University of Applied Sciences, and is responsible for data monitoring. Safety and data adequacy will be monitored every 2 weeks under the supervision of the principal investigator. During monitoring visits, the monitor will:

(1) Verify the informed consent forms; (2) Conduct a source data review of key data (e.g., primary and secondary endpoints, adverse events); (3) Discuss any open questions that have arisen during data management. Additional regular teleconferences and meetings will be held as needed to ensure compliance with appropriate quality standards and timelines.

### Adverse event reporting and harms {22}

The interventions in this trial are expected to carry low risk. Potential adverse events related to the use of the passive back-support exoskeleton may include transient discomfort, pressure, friction, or skin irritation at points of force transmission (e.g., shoulders or hips), as well as musculoskeletal soreness associated with adaptation to wearing the device. Improper adjustment of the exoskeleton to individual body proportions may increase the likelihood of such events.

To minimize these risks, a lightweight and ergonomically adjustable exoskeleton model will be used that does not restrict the user’s range of motion. Participants will receive comprehensive initial training on correct adjustment and use of the exoskeleton, with regular checks by trial staff to ensure proper fit and safe use.

Adverse events (AEs) are defined as any unfavorable or unintended signs, symptoms, or injuries occurring during the study period, regardless of whether they are considered related to the intervention. This includes events potentially related to changes in work behavior during trial participation (e.g., musculoskeletal complaints, minor injuries, or falls occurring during routine work activities). Serious adverse events (SAEs) include events that result in death, life-threatening conditions, hospitalization, persistent or significant disability, or are otherwise considered medically serious.

All AEs and SAEs, whether solicited or spontaneously reported, as well as any unintended effects occurring from enrollment until the end of the trial, will be documented. Documentation will include onset, duration, severity, management, outcome, and the investigator’s assessment of relationship to exoskeleton use. Serious adverse events will be reported to the responsible ethics committee within 24 h of the research team becoming aware of the event.

